### Assessment of Credibility

The Credibility Assessment Questionnaire is applied to assess the reliability and credibility of the trial, including the selection of the control group, the implementation of the blinding method, and the details of electroacupuncture treatment. The Credibility Assessment Questionnaire is used in electroacupuncture trials to improve the accuracy and repeatability of the trials. We will ask participants in this trial to rate the following questions on a 6-point scale: (1) How confident are you that this treatment can alleviate your complaints?; (2) If your friends also have similar complaints, how confident would you be in recommending this treatment method to them?; (3) How logical do you think this treatment is?; and (4) How successful do you think this treatment is in reducing other complaints? [45].

### Expectancy

After participants receive treatment, we expect that patients in the treatment group will have a significant improvement in sleep complaints compared with those in the sham electroacupuncture group, which will be reflected in the changes in outcome measurements. Electroacupuncture has shown certain positive effects on postoperative insomnia in patients with spinal cancer. It can be part of a comprehensive treatment plan in conjunction with other medications or nonpharmacological treatments to enhance therapeutic effects. All treatments should be carried out within a safe range to ensure the safety of electroacupuncture.

### Data Security and Monitoring

We will establish an independent DSMB to monitor whether the study design meets guideline standards to ensure the rigor of the trial. The committee consists of 5 members from different fields. Members of the DSMB must declare that there are no conflicts of interest to ensure the independence of their decisions. The DSMB will periodically review the accumulated data from clinical trials, assess the risks and benefits during the trial process, and ensure the safety of the patients. Based on the review of the data, the DSMB can advise the researchers to continue, modify, or suspend the trial. If serious AEs occur, they have the right to suspend or terminate the trial.

### Statistical Methods

#### Statistical Analysis Plan Documentation

A detailed statistical analysis plan (SAP) will be developed before data lock and unblinding, which will include additional technical details such as sample size justification, variable coding rules, and detailed analysis steps. The SAP will be signed by the principal investigator and statisticians (CJ, MY, XP, JZ, YC, FZ, JM, and DW) and will be available upon request from the journal or regulatory authorities.

#### Analysis of Primary and Secondary Outcomes (SPIRIT Item 20a)

##### Primary Outcome Analysis

The primary outcome is the change in PSQI total score from baseline (wk 0) to posttreatment (wk 4). ANCOVA will be used to compare the between-group difference in PSQI score changes, with baseline PSQI score, age, gender, tumor type, and participating center as covariates. This method can adjust for potential confounding factors and improve the statistical efficiency of the analysis.

##### Secondary Outcome Analysis

Actigraphy indicators (SOL, TST, sleep efficiency, WASO, and number of sleep awakenings): Between-group comparisons of changes from baseline to posttreatment (wk 4) and follow-up (wk 12) will be performed using ANCOVA, with corresponding baseline values and the same covariates as the primary outcome.

ISI, SOSGOQ 2.0, and PHQ-9 scores: Similar to the primary outcome, ANCOVA will be used to compare the between-group differences in score changes at each time point. If the data do not meet the normality assumption, nonparametric tests (Mann-Whitney *U* test for between-group comparisons and Wilcoxon signed-rank test for within-group comparisons) will be used as alternatives.

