### Randomization and Allocation Concealment

The random allocation scheme for this trial will be generated by The Clinical Research Center of Shanghai Municipal Hospital of Traditional Chinese Medicine, Shanghai University of Traditional Chinese Medicine. We will use stratified block randomization with centers as a stratification factor for group inclusion. When blocks are used up, centers will inform the data management center for replenishment. Independent investigators will place the treatment assignment code in consecutively numbered opaque envelopes based on the order of patients’ visits. All participants will be informed that they have the same probability of being assigned to the electroacupuncture group or the sham electroacupuncture group. Participants and researchers will not know the grouping in advance. To ensure the reliability of the research, all researchers will strictly abide by the principle of departmental separation and receive standardized training before implementation.

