#### Missing Data Handling

MI with 20 imputed datasets will be used to handle missing outcome data in the ITT analysis. The MI model will include the primary outcome, secondary outcomes, baseline characteristics, and variables associated with missingness (eg, treatment group, participating center, and adherence to treatment). For the per-protocol analysis, only complete cases will be included.

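### For ISI, SOSGOQ 2.0 and PHQ-9, the non-normality fallback replaces adjusted ANCOVA with an unadjusted Mann-Whitney test: covariate and centre adjustment is lost, and power may be too

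*Protocol article*

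**What the plan says.** Under Secondary Outcome Analysis, the paragraph on ISI, SOSGOQ 2.0 and PHQ-9 follows the primary analysis: "ANCOVA will be used to compare the between-group differences in score changes at each time point". The primary model is ANCOVA "with baseline PSQI score, age, gender, tumor type, and participating center as covariates", and Primary Outcome Analysis gives the reason: "This method can adjust for potential confounding factors and improve the statistical efficiency of the analysis". Randomization and Allocation Concealment specifies "stratified block randomization with centers as a stratification factor".

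The same secondary-outcome paragraph then sets a switch: "If the data do not meet the normality assumption, nonparametric tests" take over, listed as "Mann-Whitney *U* test for between-group comparisons and Wilcoxon signed-rank test for within-group comparisons". The switch is written only there. It is not stated for the primary PSQI analysis or in the separate actigraphy paragraph.

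**The concern.** The fallback is a stated rule, not a detail left open, and it conflicts with the plan's own reasoning. Adjustment is chosen for efficiency and randomisation is stratified by centre, yet the fallback carries neither covariates nor centre.

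The quantity reported would also depend on the data. Because the analysis is run separately at each time point, one scale could be reported as an adjusted difference in scale points at one visit and as an unadjusted rank comparison at another, and the three scales could differ from each other.

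Finally, "Wilcoxon signed-rank test for within-group comparisons" does not compare electroacupuncture with sham. Patients enter soon after surgery, when the article says sleep is most disturbed, and with PSQI above 11. Improvement in both arms through recovery and regression to the mean is therefore plausible whatever the treatment does.

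**Working it through.** **What each analysis adjusts for**

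| | ANCOVA as planned | Fallback |
|---|---|---|
| Baseline score | regression covariate | subtracted only, in the change score |
| Age, gender, tumour type | yes | no |
| Centre (stratification factor) | yes | no |
| Reported effect | adjusted mean difference | rank comparison |

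**Inputs.** The article gives no effect, SD, baseline correlation or power for the three scales, so there is no stated figure to reproduce. I borrow the PSQI planning values from Sample Size Calculation: difference 1.8, SD 3.9, so 1.8/3.9 = 0.46 SD, with two-sided α = 0.05. Sizes are 98 per arm (all randomised) and 98 × 0.8 = 78 per arm (after the stated 20% dropout). The baseline to follow-up correlation ρ is assumed to be 0.3, 0.5 or 0.7, with equal SDs at both times.

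**Near-normal data, formula.** The residual variance under ANCOVA is SD²(1−ρ²). The variance of a change score is 2·SD²(1−ρ). Mann-Whitney has efficiency 3/π relative to the t test under normality. Its efficiency on change scores relative to ANCOVA is therefore (3/π)(1+ρ)/2:
- ρ = 0.3: 0.955 × 0.65 = 0.62
- ρ = 0.5: 0.955 × 0.75 = 0.72
- ρ = 0.7: 0.955 × 0.85 = 0.81

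Power is Φ(1.8/(s√(2/n)) − 1.96), with s = 3.9√(1−ρ²) for ANCOVA, and with s = 3.9√(2(1−ρ)) and n × 3/π for Mann-Whitney.

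| n per arm | ρ | ANCOVA | Mann-Whitney on change | Loss (points) |
|---|---|---|---|---|
| 98 | 0.3 | 92.3% | 76.1% | 16 |
| 98 | 0.5 | 96.2% | 88.4% | 8 |
| 98 | 0.7 | 99.5% | 98.3% | 1 |
| 78 | 0.3 | 85.6% | 66.3% | 19 |
| 78 | 0.5 | 91.4% | 80.4% | 11 |
| 78 | 0.7 | 98.1% | 95.3% | 3 |

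Simulation of normal data at 78 per arm agrees: 83.9% against 64.3% at ρ = 0.3 (19.6 points) and 90.8% against 80.0% at ρ = 0.5. If 3.9 is read instead as the SD of change, the losses are 6 to 10 points at 98 per arm and 7 to 14 at 78, inside the same range.

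**Non-normal data, where the switch would operate.** Simulation with five centres, 98 per arm, 1,500 trials per setting. Values are for ρ = 0.3 / 0.5 / 0.7. In the first two rows the scores are rounded integers cut off at the scale limits, and results are restricted to trials where a Shapiro-Wilk check (an assumed trigger) failed.

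| Data | ANCOVA | Mann-Whitney on change |
|---|---|---|
| Mid-scale 0-28 | 92 / 97 / 100% | 75 / 90 / 98% |
| Floor-heavy 0-27 (means 8 at baseline, 4 at follow-up under sham) | 87 / 95 / 97% | 61 / 72 / 88% |
| Exponential residuals | 92 / 96 / 99% | 85 / 95 / 99.9% |
| Lognormal residuals | 92 / 95 / 99% | 85 / 95.5 / 99.9% |

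A second set of floor-heavy trials gave 89/92/98% against 60/72/89%, a loss of 29, 20 and 9 points. With heavy-tailed (t, 4 df) residuals at ρ = 0.5 the figures are 96% and 94%.

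**Does non-normality force a switch?** At ρ = 0.5, type I error under normal, exponential and lognormal residuals was 4.7% to 5.5% for every method, ANCOVA included.

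**If ranks are wanted.** With exponential residuals, rank ANCOVA (ranked outcome, adjusted for ranked baseline and centre) reached 99/99.7/99.9%, against 85/95/99.9% for the unadjusted test. It was at least as good at every correlation.

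**The case against.** The strongest reply is that the rule fires only when data are not normal, so power computed on normal data does not describe the trial after a switch. Under strong skew the loss disappears. That stands. A reader might infer from the normal-data figures that the fallback loses substantial power in general, or is always the weaker method. The exponential and lognormal results at correlation 0.5 or more contradict this, although bounded scores that trigger the switch still show losses.

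It also stands that the effect size belongs to another outcome, that the correlations are assumed, and that 78 per arm counts completers while the plan states "MI with 20 imputed datasets will be used to handle missing outcome data in the ITT analysis". The figures for 98 per arm address this last point only roughly, since imputation does not restore the lost information in full.

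A reader might further infer that the fallback ignores baseline altogether. It does not, since the analysed quantity is a change score. Nor do the documents support the inference that efficacy will be claimed from within-group change: the Results section and the anticipated findings frame the comparisons as between the two groups. How normality is judged, and how rank results are combined over imputations, may be left to the analysis plan still to be written, so neither is counted here.

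Finally, validity is not shown to suffer. Type I error stays near 5%, and the outcomes are secondary and to be interpreted cautiously. This limits how much the point matters, but does not give a reason to keep an unadjusted fallback.

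**Conclusion.** The point holds for ISI, SOSGOQ 2.0 and PHQ-9 only. The fallback as written gives up regression adjustment for baseline, age, gender, tumour type and centre, and changes the reported effect on a data-dependent trigger. That part follows directly from the text and contradicts the article's own efficiency rationale.

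The power consequence is conditional. Under the borrowed 0.46 SD and correlations of 0.3 to 0.7, the loss is roughly 1 to 20 points for near-normal data and about 9 to 29 points for floor-heavy bounded scores. It is nil or slightly reversed for strongly skewed residuals at correlation 0.5 or more. The documents cannot say which case will apply. The primary PSQI conclusion is untouched. The change is worth making before the analysis plan is signed, but it does not threaten the trial.

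**What to change.** Replace the fallback sentence. Keep the covariate-adjusted ANCOVA as the main between-group analysis of the three scales whatever the distribution, with heteroscedasticity-robust (HC3) or bootstrap confidence intervals. If a rank method is wanted for non-normal data, pre-specify a baseline-adjusted, centre-stratified one, for example rank ANCOVA, in place of the unadjusted Mann-Whitney test. Drop the within-group Wilcoxon tests or label them descriptive.

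The cost is one sentence in the plan and slightly more analysis work. The article describes both recruitment and the detailed analysis plan as still to come, so the change can be made before any data are seen.

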### Additional Analyses (SPIRIT Item 20b)

#### Subgroup Analysis

Predefined subgroup analyses will be conducted based on age ( ≤65 y vs >65 y), sex (male vs female), and tumor type (solid tumor vs hematological tumor) to explore whether the efficacy of electroacupuncture varies across different subgroups. Interaction terms between treatment group and subgroup variables will be added to the ANCOVA model to test for subgroup effects.

#### Sensitivity Analysis

To verify the robustness of the primary outcome results, sensitivity analyses will be performed by excluding participants who used hypnotic drugs during the study period and by using different imputation methods for missing data (eg, last observation carried forward vs multiple imputation [MI]).

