#### Exclusion Criteria

First, participants diagnosed with severe cardiovascular, hepatic, renal, hematopoietic, immune system diseases, or psychiatric disorders. These diseases may affect the safety of electroacupuncture treatment or interfere with the evaluation of study outcomes.

Second, those who have a history of other malignant neoplasms or concurrent other malignant tumors. Multiple tumors may lead to complex clinical symptoms and poor prognosis, which may confound the effect of electroacupuncture on insomnia.

Third, participants’ acupuncture area affected with skin infection, ulcer, and sores. These skin conditions may increase the risk of infection after acupuncture and affect the implementation of treatment.

Fourth, those who have mental disorders or sequelae of cerebral infarction leading to inability to take care of oneself or cooperate with treatment. Participants need to cooperate with acupuncturists during treatment and complete self-assessment scales, so good compliance is required.

Fifth, those who have consciousness, intelligence, language comprehension, and expression impairments. These impairments will affect the collection of outcome indicators (such as self-assessment scales).

Sixth, those who have sleep apnea syndrome. This disease is an independent cause of sleep disturbance, which may interfere with the evaluation of the efficacy of electroacupuncture on postoperative insomnia.

Seventh, those who have taken any sleeping pills, antidepressants, or antipsychotics within the past 2 weeks. These drugs may affect sleep status and lead to false results in efficacy evaluation.

Eighth, history of shift work in the past 6 months.

Finally, participants having chronic insomnia disorder (insomnia lasting ≥3 months) before SM surgery.

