### Intervention

All study participants will be randomly assigned to either the electroacupuncture group or the sham electroacupuncture group in a 1:1 ratio, receiving treatment 3 times per week for 4 weeks. At the same time, we will keep records of actigraphy for patients at week 0, week 1, week 2, week 3, and week 4. Allocation of participants will be conducted by a licensed acupuncturist with more than 2 years of clinical experience. Except for the acupuncturists, the study investigators, participants, outcome assessors, study staff, and statisticians will all be blinded to the allocation. Before treatment, we will perform skin sterilization for patients. If patients experience severe physical discomfort due to insomnia, we will prescribe appropriate medication based on their conditions. During the medication period, we will strictly record the name, dosage, and administration method. Relevant investigators will also record the medication taken by patients on a CRF.

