### Assessments and Outcomes Measurement

#### Primary Outcome

The PSQI will be the primary outcome of this trial. The cross-cultural adaptation of PSQI into simplified Chinese was successful, with good reliability and validity for comprehensively evaluating the sleep quality of patients with insomnia [31]. Furthermore, PSQI is widely used to assess the effect of cancer treatment on sleep quality in patients with cancer. PSQI comprises 19 self-assessment items and is composed of 7 subscales, including sleep quality, falling asleep time, sleep duration, sleep efficiency, sleep disorders, hypnotic drug use, and daytime dysfunction. Each component is scored on a scale of 0‐3, and the total scores of PSQI range from 0 to 21. The higher the patients’ score, the worse their sleep quality and the more severe the sleep disorders, and vice versa. The primary outcome is defined as the change in PSQI total score from baseline (wk 0) to posttreatment (wk 4).

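### Excluding patients who took hypnotics after randomisation, and carrying the baseline PSQI forward, are poor robustness checks of the primary result; the primary analysis itself is unaffected

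*Protocol article*

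**What the plan says.** The Sensitivity Analysis section gives the purpose as follows: "To verify the robustness of the primary outcome results". Two analyses serve it. In the first, "sensitivity analyses will be performed by excluding participants who used hypnotic drugs during the study period". The second varies the imputation method, with "last observation carried forward vs multiple imputation" as the example.

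Four other places bear on this:

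- **Intervention:** "If patients experience severe physical discomfort due to insomnia, we will prescribe appropriate medication based on their conditions". The medication taken is recorded on the case report form.
- **Exclusion Criteria:** the trial excludes "those who have taken any sleeping pills, antidepressants, or antipsychotics within the past 2 weeks". Hypnotic use during the study is therefore new use after entry.
- **Primary Outcome:** the PSQI components include "sleep disorders, hypnotic drug use, and daytime dysfunction", each scored 0 to 3. The endpoint is the change in total score from week 0 to week 4.
- **Table 1:** PSQI is scheduled at week 0 and next at week 4, with nothing in between.

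The primary analysis is ANCOVA in the ITT population, with 20 imputed datasets for missing outcomes.

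**The concern.** A sensitivity analysis should put the primary question again under different assumptions. The exclusion does something else. It conditions on an event after randomisation that the protocol links to severe insomnia and that is scored inside the endpoint. The patients removed tend to be the worst sleepers. If electroacupuncture works, more of them come from the sham arm, so the remaining groups are no longer comparable by randomisation.

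The LOCF example has a different weakness. With no PSQI between baseline and week 4, the last observation is the baseline value, so every patient with a missing week-4 score is given a change of exactly zero. These patients enter 1 to 2 weeks after surgery with PSQI above 11. Some recovery is plausible, and zero is not a neutral choice.

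What is at stake is the statement about robustness. A real 1.8-point effect could look fragile only because of how the check is built, and agreement with the primary result would say little in its favour.

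**Working it through.** The plan gives no figure for these analyses, so there is none to reproduce.

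**Inputs from the protocol (Sample Size Calculation):** difference δ = 1.8, SD σ = 3.9, dropout 20%.

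**Assumptions not in the documents:** sham rescue rate p of 10, 20 or 30%; a correlation ρ between the severity that triggers rescue and the week-4 outcome; one rescue threshold for both arms; no effect of the drug on PSQI.

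**1. Exclusion of hypnotic users**

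Let a₀ = Φ⁻¹(1 − p) and a₁ = a₀ + ρδ/σ, and let λ(a) = φ(a)/Φ(a). Among patients who stay below the rescue threshold, the expected difference is

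δ − ρσ[λ(a₀) − λ(a₁)].

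Worked case, ρ = 1 and p = 20%: a₀ = 0.842, a₁ = 0.842 + 1.8/3.9 = 1.303, λ(a₀) = 0.350, λ(a₁) = 0.189. The result is 1.8 − 3.9 × (0.350 − 0.189) = 1.17.

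| Sham rescue | ρ = 1: estimate (loss) | ρ = 0.6: estimate (loss) |
|---|---|---|
| 10% | 1.39 (23%) | 1.64 (9%) |
| 20% | 1.17 (35%) | 1.56 (14%) |
| 30% | 1.00 (44%) | 1.50 (17%) |

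At ρ = 1, the implied rescue in the active arm is 4, 10 and 16%. With δ = 0 and one common threshold, a₁ = a₀ and the bias is zero.

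**2. Would missing-at-random (MAR) imputation of hypnotic users repair this?**

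This was simulated under ρ = 1. Users' week-4 values were set to missing and imputed from arm and baseline (assumed baseline correlation 0.4). The estimates were 1.44, 1.24 and 1.07 at 10, 20 and 30% sham rescue. Exclusion adjusted for the same covariates gave 1.44, 1.25 and 1.08. The bias is practically the same, because users' values are drawn from non-users.

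**3. LOCF**

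Let m be the mean improvement under sham, d₀ the sham dropout and d₁ the active dropout, and assume that dropouts would have improved like completers. LOCF then estimates

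(m + δ)(1 − d₁) − m(1 − d₀).

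- Dropout 20% in both arms: 1.8 × 0.80 = 1.44, whatever m is.
- No true effect, sham 25% and active 15%, m = 4 (assumed): 4 × (0.85 − 0.75) = +0.40. For m = 3 to 5 the range is +0.30 to +0.50.
- The same dropout rates reversed: −0.40 at m = 4.
- No true effect and equal dropout: 0.

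**The case against.** The best defence is that nothing central depends on these analyses. The primary analysis keeps all randomised patients and uses MI. LOCF appears only as an example set beside MI, and the article defers detailed steps to a separate analysis plan. All of that stands.

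Several stronger readings are tempting, and the documents do not support them:

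- **That the primary result is compromised.** It is not. No primary estimate, test or sample size changes.
- **That these are the only checks.** A per-protocol analysis is also planned, as a secondary analysis. It is complete-case and also selected after randomisation, so it does not fill the gap, but it exists.
- **That both analyses are always biased.** With no effect, equal hypnotic use and equal dropout, the bias is zero. In the model above, exclusion pulls a true effect towards the null.
- **That exclusion would create a difference out of nothing.** This needs different hypnotic use in the two arms despite identical outcomes. For example, 30% sham against 20% active would give 0.34 points (ρ = 0.6) to 0.57 points (ρ = 1) against electroacupuncture. One common severity threshold does not produce that split, and the documents give no mechanism for thresholds that differ by arm.
- **That nothing departs from MAR.** LOCF does, by assuming no improvement. It is crude and has a single value, but it is a departure. The absence of a tipping-point analysis from an article is not in itself a defect.
- **That a loss of 23 to 44% is to be expected.** This is the extreme case, in which the week-4 outcome fully determines rescue. Rescue is given earlier and for discomfort, so a looser link is more realistic.

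The Intervention section also speaks of appropriate medication without naming hypnotics. The Sensitivity Analysis section nevertheless presupposes hypnotic use during the study, and this is the route to it that the protocol describes.

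**Conclusion.** The point holds for the two supportive analyses as stated. Excluding hypnotic users selects on a consequence of poor sleep that is also part of the PSQI score, so the result is not a like-for-like test of the ITT estimate. Under the protocol's own effect of 1.8 and SD of 3.9, the attenuation is about 9 to 17% (ρ = 0.6) and at most 23 to 44% (ρ = 1), for sham rescue of 10 to 30%. The rescue rates and the correlations are assumptions.

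LOCF here means baseline carried forward. It gives 1.44 instead of 1.8 at 20% dropout in both arms, and it can err in either direction when dropout differs between arms.

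The point is worth correcting, but it is of moderate weight because the primary ITT analysis with MI is untouched.

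**What to change.** 1. **Hypnotic use.** Keep all randomised patients in this sensitivity analysis. Beside the primary analysis, report a composite handling in which hypnotic users are assigned no improvement, and tabulate hypnotic use by arm. The composite answers a different question, since starting a hypnotic counts as failure, and should be labelled so.
2. **If the exclusion is kept,** call it exploratory and do not present it as a check of robustness.
3. **Do not rely on MAR imputation of hypnotic users alone,** because it reproduces most of the exclusion bias. Use it only with a delta adjustment.
4. **Missing week-4 PSQI.** Replace the LOCF example with delta-adjusted or reference-based MI over a stated range of deltas, and report the value at which the conclusion would change.

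The cost is a change of wording and some extra programming. No new data are needed, because medication is already recorded on the case report form. Rescue care is unchanged. The analysis plan is still to be written before data lock, so the change can be made there and in the protocol.
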